## Abstract

*Introduction:* People with hyperkinetic movement disorders, including dystonia, experience often painful, involuntary movements affecting functioning. Seating comfort is a key unmet need identified by families. This paper reports a protocol to assess the feasibility and preliminary evidence for the efficacy of dynamic seating to improve functional outcomes for young children with dystonic cerebral palsy (DCP). *Design:* A series of single-case experimental design N-of-1 trials, with replications across participants, with a random baseline interval, and one treatment period (*n* = 6). *Methods*: Inclusion criteria: DCP; 21.5 cm < popliteal fossa to posterior sacrum < 35 cm; Gross Motor Function Classification System level IV–V; mini-Manual Ability Classification System level IV–V; difficulties with seating. *Intervention:* Trial of the seat (8 weeks), with multiple baseline before, during and after intervention and 2 month follow up. The baseline duration will be randomised per child (2–7 weeks). *Primary outcomes:* Performance Quality Rating Scale; Canadian Occupational Performance Measure; seating tolerance. The statistician will create the randomization, with allocation concealment by registration of participants prior to sending the allocation arm to the principal investigator. Primary outcomes will be assessed from video by an assessor blind to allocation. *Analysis:* Participant outcome data will be plotted over time, with parametric and non-parametric analysis including estimated size effect for N-of-1 trials.

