### 3.7. Blinding and Blind Rating

Due to the nature of the intervention (a dynamic seat), children, parents and the visiting occupational therapist will not be blinded to the randomised baseline period allocation. The investigators will assess all children before randomisation takes place. Primary outcome measures will be administered and videoed by a member of the research team. Raters of these video-recorded assessments will be blind to the time of assessment.

Research therapists will assess all children at each assessment time point, using video, with subsequent ratings performed by trained blind assessors. Primary and secondary outcome measures will be videoed for subsequent rating by trained independent raters, blind to the time of assessment in relation to treatment. The order of video segments will be randomised before being collated for rating. Metadata, including date, will be removed from the videos to maintain blindness.

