### 3.10. Primary Outcomes

There will be three primary outcome measures. Two complementary co-primary objective outcome measures will be employed: the first one will be a subjective rating scale to explore parents/carers perceived performance and satisfaction on a number of self-selected goals using the Canadian Occupational Performance Measure (COPM) [17]. Secondly, the Performance Quality Rating Scale (PQRS) [18] will be used to measure the individual goals selected for the intervention and will be blind-rated. Further, seating tolerance will be objectively measured using sensors attached to the chair that will capture the duration and frequency of its use throughout the baseline and intervention and follow-up periods.

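### The abstract and section 3.7 claim blind video rating for all primary outcomes, but the co-primary COPM is an unblinded parent/carer rating

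*Protocol article*

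**What the plan says.** The abstract lists the primary outcomes as "Performance Quality Rating Scale; Canadian Occupational Performance Measure; seating tolerance" and states "Primary outcomes will be assessed from video by an assessor blind to allocation". No outcome is excepted.

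Section 3.7 widens the claim: "Primary and secondary outcome measures will be videoed for subsequent rating by trained independent raters". It adds that these raters will not know when, relative to treatment, a recording was made. The same section says that "children, parents and the visiting occupational therapist will not be blinded to the randomised baseline period allocation".

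Section 3.10 opens with "Two complementary co-primary objective outcome measures will be employed" and continues in the same sentence that "the first one will be a subjective rating scale to explore parents/carers perceived performance and satisfaction on a number of self-selected goals"; this first measure is COPM. PQRS, the second, "will be used to measure the individual goals selected for the intervention and will be blind-rated". Seating tolerance is to be recorded by sensors on the chair.

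**The concern.** Blinding of the outcome assessor is the main safeguard the article offers against expectation in an open intervention, so its scope has to be stated correctly. COPM is a co-primary measure. The parents choose the goals, know which seat the child is using, and supply the rating. A blind rater working from video cannot replace a parent's own view of performance or satisfaction.

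The issue is sharper for COPM than for PQRS because of timing. Table 1 shows PQRS repeated at every baseline and intervention week, but COPM only at b1, p2 and f2. With a single baseline value, COPM gains little from the randomised baseline length or from repeated measurement. The protection the text claims for it is blind rating, and it does not have that.

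Section 2.3 uses the primary outcome measures to judge whether the seat is associated with better performance on parent-identified goals, and section 2.2 says the evidence will inform a full-scale randomised trial. A reader who relies on the abstract would take a COPM improvement as blind-rated.

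**Working it through.** There is no stated figure to reproduce and no formula applies. The check compares the general blinding claim with what the article says about each measure.

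| Measure | Role | How the score arises | Described as blind-rated from video? |
|---|---|---|---|
| PQRS | Co-primary | Independent observer scores video clips (3.10, 3.17) | Yes |
| COPM | Co-primary | Parent/carer's own subjective rating (3.10); parents not blinded (3.7) | No; the definition rules it out |
| Seating tolerance | Third primary | Pressure switch and data logger (3.10, 3.18) | No; no human rater |
| Sleep quality | Secondary | Wrist or ankle motion sensor (3.18, Table 2) | No; no human rater |
| PedsQL | Secondary | Inventory of levels of difficulty (3.11); respondent not stated | Not described as such |

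1. **Does any passage make COPM a blind-rated measure?** No. Section 3.10 attaches blind rating to PQRS alone. Section 3.17, under Outcome Evaluation, names PQRS and no other measure as scored by an independent observer from video. Section 3.16 plans the rater reliability coefficient for PQRS only.

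2. **Could both statements be true of COPM?** Only if an independent rater produced the COPM score. Section 3.10 says the score expresses parents' or carers' perception. Filming the interview, or having a third party administer it, would not change whose judgement is recorded.

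3. **Is the wording in 3.10 consistent?** No. One sentence calls the pair objective and its first member subjective.

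4. **Count.** Co-primary measures with blind video rating: 1 of 2. All primary outcomes with blind video rating: 1 of 3. The two that lack it differ in kind: COPM has an unblinded human rater, and seating tolerance has no rater. The rater-blinding concern among the primary outcomes is therefore COPM alone.

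**The case against.** The strongest reply is that the methods text already settles the matter. Sections 3.10, 3.16 and 3.17 tie blind video rating to PQRS, 3.10 calls COPM subjective, and 3.7 openly says parents are not blinded. A careful reader can work out what COPM is, and no procedure depends on the over-broad sentences. This stands to the extent that the defect is one of description. Using a parent-rated COPM is a legitimate choice. It does not remove the point: the abstract is what most readers see, and 3.7, the section on blinding, repeats the claim and extends it. Nor is this a detail left to a fuller protocol or the SAP, since neither could make the published sentences true.

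A reader might infer more than the documents support:

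- **That two of three primary outcomes are exposed to rater bias.** Seating tolerance is not video-rated, but a pressure switch has no expectation to bias. The same holds for sleep.
- **That PedsQL is also an unblinded parent report.** Section 3.11 does not say who completes it. Its description as an inventory, and the mention of questionnaires in 3.20, suggest it is not video-rated, but no more than that.
- **That a false-positive probability can be attached.** The article gives no size for any expectation effect. It plans means and 95% confidence intervals (3.19), states no success rule, and says in 3.5 that the sample is not based on power for group effects. Any such figure would also describe open-label reporting in general and would be unchanged by correcting the wording.
- **That COPM should count only if PQRS moves the same way.** That would be a new evidential rule on which statisticians could disagree. Section 3.10 presents the two measures as complementary, and Table 1 schedules COPM at f2 but shows PQRS ending at p1.

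**Conclusion.** The point holds as a contradiction within the article. The abstract and 3.7 state a protection against bias that one of the two co-primary measures, by its own definition, cannot have, and 3.10 adds to this by calling that measure objective. It deserves correction because it changes how a COPM gain may be read: as open-label evidence from parents who know which seat is in use.

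The conclusion rests only on the article's descriptions of COPM and of parents' awareness, and needs no assumption about how large any expectation effect would be. It does not show that COPM is a poor outcome, that the sensor measures are biased, or that any particular result would be wrong. It takes the blind rating of PQRS as stated and does not test whether that masking would succeed on video.

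**What to change.** - **Abstract and 3.7:** limit the statement on blind video rating to PQRS and any other measure actually scored from video, naming each one. Say that seating tolerance and sleep quality come from sensors.
- **Section 3.10:** stop describing COPM as objective and label it an unblinded parent/carer rating.
- **Reporting:** present any COPM change as open-label evidence, distinct from the blind-rated PQRS.

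The change is to wording only; design, visits, sample size and analysis stay as they are. Its cost is that the stated blinding becomes less favourable.

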## 1. Introduction

Dystonia is a neurological syndrome that differs from spasticity and it is characterised by involuntary, patterned, sustained, or repetitive contractions of opposing muscles, resulting in abnormal twisting body movements and abnormal postures [1].

Children with dystonia experience involuntary movements throughout their waking day, and this affects all areas of functioning defined in the International Classification of Function (ICF) [2]. Dystonic movements are often triggered by attempts to move [3], limiting the ability of the child to participate at the very moment they wish to do so. It is often painful and causes discomfort. This may lead to frustration and distress, which further compounds the severity of the involuntary movements, causing a toxic feedback loop. Gimeno et al. [4] reported and ranked functional concerns identified by families and young people with dystonic movement disorders: first was pain affecting function, and access to assistive technology; second, dressing, hygiene and handling tools (including feeding); and third, participation in outdoor activities. Access to assistive technology and pain were highlighted as the highest priority concern(s) for more than half the group. In their systematic review of interventions for children with cerebral palsy, Novak et al. [5] identified a pronounced lack of high-quality research in assistive technology to support activity and participation. Thus, the support of activity and participation is a high priority for work in this under-researched area.

Dynamic seating is a type of seating that enables the occupant to move while seated. Dynamic seats are used in a wide variety of contexts, including vehicles and offices. However, in this context, dynamic seating is designed to facilitate the movements of disabled people, while providing postural support. There are multiple dynamic seats on the market that are designed to be used by children with cerebral palsy, however they differ from the seat that is the subject of this trial. Some seats (the R82 x:Panda for example) simply have a sprung backrest, hinged about an axis close to the child’s hips, and are able to move backwards if leaned upon. Others, such as the Netti or Interco Aktivline have more complex mechanisms that enable the user to extend their hips and knees. There is little published research evaluating dynamic seating for people with dystonia [6,7].

The present seat provides postural support for children with dystonic cerebral palsy and whole-body involuntary extensor movements. It enables the occupant to independently extend their hips, knees and spine while remaining seated. The seat’s supports yield to powerful involuntary movements and support voluntary movements through pivots that are aligned with the occupant’s joints and are gently sprung. The principal weight-bearing support is a saddle on which the child sits. The seat consists of a chassis to which is attached two independently hinged leg supports and a hinged backrest. The child’s thighs are supported independently by moveable supports that are sprung and hinged on an axis aligned with the child’s hip joints. The child’s feet are supported by a pair of foot supports that are attached to the leg supports through hinged joints aligned with the child’s knees. Each foot support is sprung, able to move independently of the other foot, and pivots about an axis aligned to the ankle joint. The back rest provides support to the child’s back, the sides of the thorax, and the head. A 4-point pelvic belt, thigh straps, ankle harnesses and a chest harness prevent the occupant from falling out of the seat.

### 1.1. Dynamic Seating Research

Initial screening of papers for a current systematic review of dynamic seating [8] has yielded only two peer-reviewed scientific studies evaluating existing commercial dynamic seats [6,7]. These seats do not accommodate asymmetric movements, yet most involuntary dystonic movements are asymmetric, and cause unwanted postural displacement in seating that enforces symmetry.

In a consultation on the project, parents were strongly supportive of the trial of an already designed new seat. They liked the minimal visual impact of the seat and emphasised the need to design the seat for easy adjustment, cleaning, transfers and transport. In regards to methodology, parents suggested that a seat should be provided for each child, and that the quantity of written feedback from parents should be minimised.

### 1.2. Why a Trial Is Needed

In July 2012, the National Institute for Care and health Excellence (NICE) spasticity guidelines [9] (which includes other co-existing motor disorders such as childhood dystonia) reviewed the effectiveness of occupational therapy and/or physiotherapy interventions. Only 14 publications were included and out of those, only one study included children with dystonic/hyperkinetic phenotype [10], with the majority of the study including children with spastic CP.

Further, the guideline states that children with CP should have timely access to equipment necessary for their management programme; for example, postural management equipment, including sitting and standing systems. It states that intervention should be focused on enhancing skill development, function and ability to participate in everyday activities, as well as preventing adverse consequences such as pain or contractures. There is no previous research that evaluates the feasibility and acceptability of the dynamic chair and that this is imperative because present guidelines highlight enhancing skill development, function and ability.

In conclusion, children with dystonic movement disorders including dyskinetic CP, and their families report sitting comfortably as one of their major concerns and challenges [4]. Difficulties with sitting amplify their difficulties participating in all areas of life. A dynamic seat that offers flexible and comfortable support may facilitate inclusion and participation and promote a more positive motor-sensory feedback loop, potentially leading to improved function and quality of life.

The proposed study will be a proof of principle using single-case experimental design (SCED) to evaluate the feasibility and potential efficacy of using a dynamic seat in children with dystonic cerebral palsy to inform future clinical trials.

## 2. Aims and Objectives

### 2.1. Purpose of the Research

The overall aim of this work is to test the feasibility of using the proposed protocol for testing the potential efficacy of a specific dynamic seat for children with dystonic cerebral palsy, for the purpose of guiding the design of a larger efficacy trial.

This study will investigate the use of the dynamic seating system on a range of activity and participation outcomes for young children with severe dystonic CP, with particular interest in achieving parent-defined functional goals, activity, participation and quality of life.

### 2.2. Overarching Study Aim

To examine the feasibility and acceptability of a clinical trial investigating the efficacy of a dynamic seating system for young children with severe dystonic cerebral palsy. The evidence will help inform a future full-scale randomised clinical trial.

### 2.3. Specific Primary Aims per Series of N-of-1 Trials

Assess variability of outcome using N-of-1 type design (between- and within-period variances) and estimate effect size (for N-of-1 trials) of treatment outcomes to inform the design of future clinical trials.Evaluate the potential efficacy of the dynamic seating system intervention at varying times (across a number of weeks) using N-of-1 type design.Assess whether dynamic seating is associated with improved individual functional performance on (parent) identified goals as measured by the primary outcome measures.Assess whether changes can be observed in secondary outcomes, including health-related quality of life.

### 2.4. Hypothesis

The use of whole-body dynamic seating can improve comfort, activity, participation, and quality of life in young children with dystonic cerebral palsy.

## 3. Method

### 3.1. Design

The proposed study design is a series of N-of-1 trials, with replications across subjects (N-of-1 plus 5 replications). For each child, there will be at least 5 baseline assessments over at least 2 weeks in their usual seating (each trial provides one data point or baseline assessment, for example, reaching forward to hit a switch is one data point/one baseline). Therefore, there will be multiple baselines within each visit session. The baseline period will be followed by an intervention assessment period of 8 weeks when they are using the dynamic seat, and then a 2 month follow-up period. The duration of the baseline will be randomised for each child and will be between 2 and 7 weeks and therefore participants with longer baselines will have a larger number of baseline data-points. The baseline period will represent treatment as usual (TAU). In this way, comparison of TAU and dynamic seating provision is possible, with each participant acting as their own control.

### 3.2. Recruitment

Participants will be recruited through Evelina London Children’s Hospital, Guy’s and St Thomas’ National Health System Trust. Additional recruitment centres providing care for children with dystonia will be enrolled only if needed to reach the target numbers.

### 3.3. Eligibility

Inclusion criteria for the study are: (a) diagnosis of dystonic cerebral palsy; (b) 21.5 cm < popliteal fossa to posterior sacrum < 35 cm; (c) Gross Motor Function Classification System (GMFCS) levels IV–V [11,12]; (d) Manual Ability Classification System (MACS)/mini-MACS levels IV–V [13]; and (e) difficulties reported with current seating.

Exclusion criteria are: (a) pure spasticity or mixed phenotype when spasticity is the dominant feature; (b) dystonia due to a neurodegenerative condition; (c) scheduled for other surgical treatments (e.g., hip surgery) in the study period; (d) scheduled to receive botulinum toxin injections during the study period; and (e) epilepsy.

### 3.4. Withdrawal of Subjects

Premature withdrawal of an enrolled participant will be considered if the child/parent expresses reluctance or appears reluctant to engage in the study, even if consent was provided at the point of recruitment. Participants will be free to withdraw at any time without giving a reason for their decision and with no consequence to their clinical care. The right to withdraw will be explained verbally and in the information sheets.

### 3.5. Sample Size

In SCED or N-of-1 design with replications across participants, sample (series) size is not based on the power to test group effects using inferential statistics, as each separate trial examines change over time within an individual. This will allow us to determine whether treatment has an effect for an individual. In N-of-1 studies, the number of replications (participants recruited) chosen after the first case is often based on pragmatic grounds related to the known heterogeneity of the clinical sample, and the number of measurements within each time period is based on the likely variability in outcome. It is recommended that N-of-1 plus 3 replications are necessary as a minimum to explore the efficacy of an intervention, but a total of 5 replications is better. Similarly, it is recommended that at least 3 assessment points are measured at baseline. Multiple baseline assessments will be made per child per week during the randomised baseline period that varies between 2 and 7 weeks.

A sample size of 6 will be sufficient to provide information on whether the intervention is effective for individuals, to examine the direction of ‘average treatment effect’ across individuals, and to provide estimates of the within- and between-subject variability of outcomes in this population. It will also allow us to obtain information on ease of recruitment and adherence to protocol.

### 3.6. Randomisation and Allocation Concealment

Treatment allocation will take place by randomisation with participants of assigned baseline length. Allocation concealment will be achieved by registration of consented participants on to a randomisation database prior to the allocation arm being sent to the principle investigator via email, and from there to the centre delivering treatment.

The trial statistician who has no direct contact with the clinical aspects of the trial or the study team will perform randomisation. Block randomisation will be performed, and a list will be generated using Stata (https://www.stata.com/). The length of each participant’s baseline period will be randomised to a non-repeating sequence of random integer durations that are between 2 and 7 weeks, where 2 weeks ≤ baseline period ≤ 7 weeks.

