#### 3.19.1. Data from SCED

To describe the impact of the intervention in the single-case experimental studies, pre-intervention and post-intervention raw scores will be examined in all outcome measures. Analysis of PQRS changes will be evaluated using an appropriate analysis for SCED. The analysis will be guided by interpretation of the visual representation of the results; whether there is auto-correlation on baseline data; and whether there is baseline trend present in the data set. We will follow the recommendations from the Single-Case Reporting Guideline in Behavioural Interventions (SCRIBE) [24]. Visual analysis will be undertaken to evaluate changes in the domains of means, levels, trends, variability, latency and consistency. This will be followed by statistical analysis of the graph which will vary depending on serial dependency. Estimated effect size will be calculated using a suitable regression approach for SCED. We will initially fit a naïve linear regression model using ordinary least squares for reference only. We will use the Tau-*U* approach as it takes into account baseline trend and is considered one of the most robust effect size methods in SCED [25].

SCED uses repeated measures and therefore provides multiple data points. The extended baseline and intervention phases will result in many data points. PQRS can be applied multiple times within the same practiced task, given it is scoring the quality of performance rather than one-off task performance [20]. Therefore, each task step within a task is assigned a data point.

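### No analysis named in the protocol uses the six randomised baseline lengths, and one transition per child supports neither a firm individual verdict nor a between-period variance

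*Protocol article*

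**What the plan says.** The design (protocol article, 3.1) is a "series of N-of-1 trials, with replications across subjects (N-of-1 plus 5 replications", and the Abstract describes it as "with a random baseline interval, and one treatment period". The phase order is the same for every child: "The baseline period will be followed by an intervention assessment period of 8 weeks when they are using the dynamic seat". Under 3.6, each child's baseline length "will be randomised to a non-repeating sequence of random integer durations that are between 2 and 7 weeks".

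Section 3.5 says that "sample (series) size is not based on the power to test group effects using inferential statistics", and goes on: "This will allow us to determine whether treatment has an effect for an individual". The first aim in 2.3 begins "Assess variability of outcome using N-of-1 type design (between- and within-period variances" and says that this is to inform future trials.

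On analysis, 3.19.1 states: "The analysis will be guided by interpretation of the visual representation of the results". It names visual analysis, an OLS fit kept only as a reference, and Tau-U, chosen because it allows for baseline trend. It also leaves a regression method for single-case data unspecified. Section 3.19 adds means and 95% confidence intervals for change, and announces a full SAP. The only consequence that 3.1 draws from baseline length is that longer baselines yield more data points.

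**The concern.** Every child goes from usual seating to the dynamic seat, never the reverse. Anything that improves with time (practice on the filmed tasks, maturation, attention to goals) therefore looks like a benefit of the seat. Section 3.15 itself concedes that the weekly goal visits could count as an intervention. The randomised, staggered start is what lets the series tell a change tied to the seat from a change tied to elapsed time. A comparison of phases within each child does not use it.

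Two statements then claim more than a single transition per child can give: that an effect will be determined for an individual, and that between-period variance will be assessed. At stake are the evidence on efficacy and the variance figures that are to be carried into a larger trial.

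**Working it through.** **Inputs from the protocol.** Six children (1 + 5; 3.1 and 3.5). Integer baselines of 2 to 7 weeks, none repeated (3.6). One baseline and one 8-week seat period per child (Abstract, 3.1). Table 1 marks PQRS and seat occupancy in every baseline and seat week, and COPM once at baseline (b1).

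**Count.** 7 − 2 + 1 = 6 lengths for 6 children, so each length is used exactly once. The protocol gives no alpha, power, effect size or SD, so there is no power figure to reproduce.

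**Smallest design-based p.**
- One child: 6 possible start weeks, 1/6 = 0.167. Reaching 0.05 would take 1/0.05 = 20 possible start weeks.
- The series: 6! = 720 assignments, 1/720 = 0.0014. With 5 children left it is 1/120 = 0.0083; with 4, 1/24 = 0.042.

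**Drift (simulation).** Assumptions: one value per week over the 10 weeks common to all children (2 + 8), independent errors with SD 1, linear drift, no seat effect, one-sided 5%. Tau-U is trend-corrected and pooled over the six children. The randomisation test takes the mean seat-minus-baseline difference over children and recomputes it for all 720 assignments.

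| Drift per week | Total over 10 visits (9 steps) | Pooled Tau-U, false positives | Randomisation test |
|---|---|---|---|
| 0.05 SD | 0.45 SD | about 18% | near 5% |
| 0.1 SD | 0.9 SD | about 37% | near 5% |
| 0.2 SD | 1.8 SD | about 79% | near 5% |

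The randomisation test also stayed at 4–6% with AR(1) correlation of 0.3 or 0.5.

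**One child.** Suppose there is no seat effect, but each period has its own random level with SD 0.5 of the residual SD (three recordings a week, nominal two-sided 5%). A child's Tau-U is then significant in 28–40% of cases across the six lengths, and in 25–39% with trend correction. With no period variation it is about 5%. The period SD is an assumption.

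**Between-period variance.** With one period per condition, the design rows for intercept, seat and period are (1, 0, 0) and (1, 1, 1). That is rank 2 for 3 parameters. Degrees of freedom between periods within a condition are (1 − 1) + (1 − 1) = 0 per child, so period and seat are aliased.

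**Power and limits of the randomisation test** (same 10-week set-up).
- Immediate shift: about 55–60% for 1 SD and about 85% for 1.5 SD.
- Effect that builds linearly over 4 weeks: about 12% and 18%.
- The 10-week window drops 0 + 1 + 2 + 3 + 4 + 5 = 15 of 6 × 8 = 48 seat weeks.
- If the seat-configuration visits c1–c2 take 1 or 2 unmeasured weeks and the data are indexed by visit number, size at 0.2 SD per week rises to about 9% or 17%.

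**The case against.** The strongest reply is that the protocol leaves room. Section 3.19.1 keeps a regression method open, visual analysis covers latency and consistency, which can include comparing staggered replications by eye, and a SAP is promised. This stands. A reader might infer that the trial never uses its randomisation or throws away the valid test; the document supports only that no analysis it names uses the baseline lengths.

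Second, Tau-U is named as an effect size, and no pooled significance test is stated. This also stands: the false-positive rates describe what would happen if Tau-U were pooled and tested. Rates near 100% can be produced, for example without trend correction at the largest drift, but the protocol gives no drift figure and one extreme case should not be reported as the result.

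Third, the 1/6 floor concerns only a randomisation test in one child. One transition does yield an individual estimate and a model-based test, and 3.5 also uses the softer wording of providing information. So it would be wrong to infer that nothing can be learned about an individual. What remains is that the word determine is too strong.

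Fourth, period is undefined. If it means week, between-week variance within a phase is estimable, as are within- and between-child variability, though imprecisely with six children. The aliasing holds for period in the usual N-of-1 sense.

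Finally, the randomisation test is no cure-all: it has little power for slow effects, is sensitive to an unmeasured gap, and cannot be applied to COPM with its single baseline value. That argues for adding it beside the planned methods, not for making it the main inference.

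**Conclusion.** The point holds in limited form and should be acted on. Six distinct baseline lengths are randomised and no named analysis uses them, while the named within-child methods are exposed to drift. The size of that exposure, roughly 18% to 79% false positives for a pooled, trend-corrected Tau-U test, rests on assumed linear drifts of 0.05 to 0.2 SD per week and on a test that the protocol does not specify. The figures 1/6, 1/720 and zero degrees of freedom follow from the design alone.

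The individual claim in 3.5 is stronger than one transition supports, because any individual estimate relies on nothing else changing when the seat arrives. The between-period aim in 2.3 cannot be met with one period per condition, whatever the SAP says, unless period is redefined as week.

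**What to change.** 1. **Section 3.19.1 or the SAP.** Keep Tau-U and visual analysis, and add one pre-specified series-level randomisation test for the repeatedly measured primary outcomes, PQRS and seat occupancy, but not COPM. Use the allocated start weeks and all 720 assignments (smallest p 0.0014), and say how withdrawals reduce the set. Index observations by calendar week since b1, counting any c1–c2 time, so that an unmeasured gap at the transition does not inflate the test under drift. State that power is about 60–85% for an immediate shift of 1–1.5 SD but only about 12–18% if the effect builds over about 4 weeks, so that a non-significant result is not read as no effect.
2. **Section 3.5.** Describe individual results as descriptive or model-based, and name the assumption that nothing else changed at the transition.
3. **Section 2.3.** Replace between-period variance by between-visit (week) and within-visit variance within each phase, plus between-child variance of the effect.

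The cost is one added analysis with no new data, a record of the calendar time taken by c1–c2, and more modest claims about individual children.
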